##### SC-VR intervention

RQ2.1 and RQ2.2: The feasibility and acceptability of the SC-VR intervention will be questioned in semi-structured experience-based interviews [35] considering the appropriateness of the VR environment to the needs of SCs, differences in comparison to SCs in presence, and whether there have to be considered specific adaptations to the VR environment.RQ2.3: Facilitator adherence will be evaluated by two independent raters for each SC-VR seminar using the SC adherence scale from the “Heidelberg study on systemic constellations” [2–5].RQ2.4: Clients’ compliance will be assessed by the percentage of seminars attempted and completed.RQ2.5: The ease and intensity of participating in both the SC and in the VR environment, and the enjoyment of the SC-VR seminar, will be assessed based on the potential cybersickness using a validated 7-item scale [36], and the level of immersion [37] in the VR experience using a validated 15-item measure. In addition, we will measure clients’ expectancy using a validated 5-item scale [38].RQ2.6: Additional identified benefits and barriers of VR for the use of SCs will be questioned in semi-structured experience-based interviews [35].RQ2.7: Finally, as part of good clinical practice, adverse events will be monitored throughout the study and considered in relation to intervention safety and potential adverse outcomes. For any adverse event during or after the intervention, psychological psychotherapists at the Center for Mental Health and Psychotherapy (ZPP) of UW/H, co-directed by [name]. [name], will be available.

##### Estimation of effect sizes

RQ3.1: The potential effect of SCs in VR to relate to the SCs versus the VR environment will be questioned in semi-structured experience-based interviews [35].RQ3.2: The estimation of effect sizes and 95% CI for change will concentrate on the proposed secondary outcome, i.e., psychological functioning (OQ-45.2), from baseline to 4-month follow-up.RQ3.3: In addition, effect sizes and 95% CI for change in the proposed secondary outcomes, i.e., systemic functioning (EXIS), psychological distress (FEP-2), motivational incongruence (INK-SF), and goal attainment (GAS), will be calculated from baseline to 4-month follow-up.RQ3.4: The proportion of clients experiencing clinically meaningful change, i.e., remission, response, deterioration, and no change, will be explored for the proposed secondary outcome (OQ-45.2)

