#### Feasibility and acceptability measures

##### Research methodology

RQ1.1 and RQ1.2: The feasibility of protocol implementation will include the ability to meet the total recruitment goal (*n* = 128), in the IG (*n* = 64) and WLG (*n* = 64) in particular. It takes the estimation of the total sample to be recruited into account, the total drop-out rate, and differential drop-out rate within the study arms at all measurement times. Data will be collected through the observation of the client flow: counting the number of interested persons who will (1) contact the recruiting office, (2) drop out by not giving consent, (3) drop out before the beginning of the SC-VR seminars, (4) start SC-VR seminar, (5) drop out during the SC-VR seminars, (6) end SC-VR seminar, (7) participate in the 2-week follow-up, (8) participate in the 4-month follow-up, (9) participate in the 8-month follow-up, and (10) participate in the 12-month follow-up. All clients must be abstained from taking part in any another SC until completion of the study. Success will be defined as the achievement of 100% of the planned sample and retaining 85% of the clients in the SC-VR intervention.RQ1.3: Outcome measure appropriateness will be assessed through the observation of missing data and the delay in answering the outcome measures. Success will be defined by missing data below 20% of the total data set and the answering of outcome measures within 3 days around the measurement date.

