#### Proposed secondary outcome measures

The *Outcome Questionnaire* (OQ-45.2) [25, 26] will be used to assess psychological functioning. The OQ-45.2 is a self reporting instrument that measures psychotherapeutic change over the previous week. Its total score (OQ-TOT) indicates symptom distress, quality of interpersonal relations, and social role performance. The OQ-45.2 features test–retest reliability of 0.84, excellent internal consistency at 0.93, sensitivity to change, and concurrent validity with a variety of self-report scales [25, 43, 44].

The *Questionnaire for the Evaluation of Treatment Progress (FEP-2)* [27] will be used for measuring psychological distress. The FEP-2 measures how persons feel over the previous week. Its total score (FEP-TOT) indicates well-being, symptom distress, interpersonal relationships, and congruence. The FEP-2 shows test–retest reliability of 0.77 (1 week) and internal consistency of 0.94. Concurrent validity and sensitivity to change were demonstrated.

The *Incongruence Questionnaire (INK-SF)* [28] will be used to measure motivational incongruence. Its total score (INK-SF-TOT) indicates approach goals (the maximization of desirable outcomes) and avoidance goals (the minimization of unwanted outcomes). One-week test–retest reliability was 0.81, and internal consistencies ranged from 0.75 to 0.91. Criterion validity was assessed using established instruments for psychopathological symptoms and quality of life.

The *Experience in Social Systems Questionnaire (EXIS)* [29] measures basic dimensions of what SCs aim to change in how clients experience themselves within their most important social and organizational systems (I-within-my-systems). The total score measures the clients’ experience in their personal systems (EXIS.pers) or organizational social systems (EXIS.org) containing the subdimensions of experiencing belonging, autonomy, accord, and confidence. The EXIS shows an internal consistency of 0.90. Concurrent validity and sensitivity to change were demonstrated.

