For *estimation of effect sizes*, we will use QCA and/or CQR to analyze information about the association of these effects to either the SCs or the VR environment, or both (RQ3.1). Because clients within groups (i.e., SC-VR seminar) may be more similar to each other than clients in different SC-VR seminars, a two-level linear regression analysis will be performed to account for potential clustering effects at higher levels (i.e., clients nested within SC-VR seminars). The intraclass correlation (ICC) coefficient from the random intercept model with clients (level 1) and SC-VR seminar (level 2) will be calculated for the proposed secondary outcome (OQ-45.2) [46]. An ICC greater than zero will indicate a clustering effect, and any statistical analysis must be adjusted for this effect. All proposed outcomes will be analyzed as intention-to-treat using mean scores (M), standard deviations (SD), and 95% CI. Missing values of less than 20% will be replaced with the conditional mean value of the four subgroups (ACs in IG, and WLG; OCs in IG, and WLG). This will be compared to per-protocol analyses. We then will use mixed-design ANOVAs (group: IG, WLG; client status: AC, OC; time: baseline, 2-week and 4-month follow-up), adjusting for baseline scores considering demography as well as outcome data. Because treatment outcome will be measured at three assessment points, within-group effects will be further analyzed by comparisons between baseline and 2-week follow-up (contrast A), and by comparisons between 2-week and 4-month follow-ups (contrast B). Effect sizes will be presented as partial eta-squared values (η^2^) and Cohen’s *d*, calculated as the difference between the means divided by the pooled standard deviation $$(d=\frac{{x}_{1}^{2}-{x}_{1}^{2}}{\frac{\sqrt{{s}_{1}^{2}+{s}_{2}^{2}}}{2}})$$. Classification of *effect sizes* will be as follows: η^2^ ≥ 0.010, small effect; η^2^ ≥ 0.060, medium effect; η^2^ ≥ 0.140, large effect; Cohen’s *d* ≥ 0.20, small effect; *d* ≥ 0.50, medium effect; and *d* ≥ 0.80, large effect [47] (RQ3.2, RQ3.3). The exploration of *reliably significant change*, i.e., the proportion of remission, response, deterioration, and no change, will be limited to the proposed secondary outcome (OQ-45.2) based on the reliable change index (RCI) [48]. We will use previously established internal consistency reliabilities to calculate the RCI [49] and Jacobson and Truax’s [48] cutoff C for the categorization of the clients’ (no) change [26–28] (RQ3.4).

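### Subgroup-mean replacement is not switched off for the RQ3.4 reliable-change classes, so a client with no follow-up OQ-45.2 score could be classed from baseline alone

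*Protocol article*

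**What the plan says.** The Estimation of effect sizes section, under RQ3.4, states: "The proportion of clients experiencing clinically meaningful change, i.e., remission, response, deterioration, and no change, will be explored". The measure is the OQ-45.2. RQ3.4 names no time point; RQ3.2 and RQ3.3 run from baseline to the 4-month follow-up.

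The Analysis section gives the method: "We will use previously established internal consistency reliabilities to calculate the RCI", combined with the Jacobson-Truax cutoff C. Proposed secondary outcome measures supplies the reliabilities: "The OQ-45.2 features test–retest reliability of 0.84, excellent internal consistency at 0.93".

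On population and missing data, the Analysis section says "All proposed outcomes will be analyzed as intention-to-treat using mean scores" (with standard deviations and confidence intervals), then "Missing values of less than 20% will be replaced with the conditional mean value of the four subgroups". The subgroups are "ACs in IG, and WLG; OCs in IG, and WLG". It adds: "This will be compared to per-protocol analyses". No other missing-data rule is given, and RQ3.4 has none of its own.

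**The concern.** Reliable change is a statement about one person: whether that person's two scores differ by more than measurement error. It needs a baseline and a follow-up score from the same client.

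A subgroup mean may be tolerable as a filler when the target is a group mean. As a filler for an individual class it is not. Each client in an arm-by-role cell without a follow-up score receives the same constant, so the apparent change is that constant minus the client's own baseline. A client who started well above the constant is counted as reliably improved, one who started well below it as deteriorated, and one in between as unchanged. Nothing about the client's course has been observed.

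At stake are the reported class proportions in a first study of this intervention. Deterioration matters most, because its true share is likely to be small and a few artificial cases are then a large fraction of it.

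**Working it through.** The protocol gives no figure for RQ3.4, so there is none to reproduce. The check covers the reliable-change step only, because neither cutoff C nor an OQ-45.2 SD is given. *Improved* below therefore covers response and remission together.

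**Inputs from the protocol**
- Internal consistency 0.93 (Proposed secondary outcome measures).
- 64 clients per arm (Design).
- Mean improvement 0.45 SD, the lower end of the 0.45–0.51 reported for the earlier in-person trial (Efficacy); 0 and 0.5 SD are also used.

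**Assumptions**
- Normal scores with equal SD of 1 at both times.
- Baseline-to-follow-up correlation r = 0.7, with 0.84 as a higher case.
- 15% of follow-up scores missing. The protocol's target is "retaining 85% of the clients in the SC-VR intervention", which concerns seminar retention and not questionnaire completion, so 15% is an illustration.
- Clients without a follow-up score resemble those with one.

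**Threshold**

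1.96 × √(2 × (1 − 0.93)) = 1.96 × √0.14 = 0.733 SD.

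**Spread of change**
- Observed clients: √(2 × (1 − r)), which is 0.775 at r = 0.7 and 0.566 at r = 0.84.
- Mean-filled clients: 1, because only the baseline varies.

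**Class shares**, with mean improvement d and change SD s: improved = 1 − Φ((0.733 − d)/s); deteriorated = Φ((−0.733 − d)/s).

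| Case | Improved | Deteriorated | No change |
|---|---|---|---|
| d = 0, mean-filled | 23.2% | 23.2% | 53.7% |
| d = 0, observed, r = 0.7 | 17.2% | 17.2% | 65.6% |
| d = 0.45, mean-filled | 38.8% | 11.8% | 49.3% |
| d = 0.45, observed, r = 0.7 | 35.7% | 6.3% | 57.9% |
| d = 0.5, mean-filled | 40.8% | 10.9% | 48.4% |
| d = 0.5, observed, r = 0.84 | 34.0% | 1.5% | 64.5% |

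With no mean change, 46% of mean-filled clients are labelled reliably changed, against 34% of observed clients. In simulation (d of 0 and 0.5; r of 0.6, 0.7 and 0.84) the filled class differed from the true class for 46–48% of such clients.

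**Whole arm at 15% missing** (0.85 × observed + 0.15 × filled)
- d = 0.45, r = 0.7, improved: 0.85 × 35.7 + 0.15 × 38.8 = 36.2%, up 0.5 points, or 0.3 of a client in 64.
- d = 0.45, r = 0.7, deteriorated: 0.85 × 6.3 + 0.15 × 11.8 = 7.2%, up 0.8 points before rounding, or 0.5 of a client in 64.
- d = 0.5, r = 0.84: improved 34.0% to 35.0%; deteriorated 1.5% to 2.9%.

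For scale, the standard error at n = 64 is √(0.357 × 0.643/64) = 6.0 points for improvement and √(0.063 × 0.937/64) = 3.0 points for deterioration.

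**The case against.** **The text does not say that filled scores enter the classification.** The replacement sentence follows the means and confidence intervals and precedes the ANOVAs; the reliable change index comes later as a separate exploration. That is fair as far as it goes. But the intention-to-treat statement covers all proposed outcomes, the OQ-45.2 is one of them, and no exception is made.

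**The 20% has no stated unit.** If it means items within a questionnaire, clients lost to follow-up are not filled at all, and the plan is merely silent on them, which an article may leave to a fuller document. This stands as a real condition on the point. Two things favour the score-level reading: the RQ1.3 success criterion measures its 20% against the total data set, and arm-by-role means suit scale scores.

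**Safeguards exist.** Drop-out by arm and missing outcome data are reported at each time, a per-protocol comparison is planned, adverse events are monitored separately, and all analyses are declared descriptive and explorative. These limit the harm and may expose the problem, but they leave the intention-to-treat proportions as they are.

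**Stronger readings that do not hold.** A reader might infer that every client lost to follow-up becomes a responder or a deteriorated case; about half would be classed as unchanged. A reader might also compare 36% response under the rule with 30% when drop-outs are not counted as responders (0.357 × 0.85 = 0.304) and call the gap the bias. That gap comes from the change of denominator. Against clients with observed scores, the distortion is about half a point.

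**Conclusion.** The point holds in a limited form. On the more natural reading of the Analysis section, the missing-data rule reaches the RQ3.4 classes and assigns individual outcomes that nobody observed. That is an invalid use of a stated rule, whatever the percentages turn out to be.

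Its effect on the reported proportions is modest: under a point for either class in the 0.45 SD, r = 0.7 scenario, well inside one standard error. The relative effect on deterioration grows with the correlation, and the rate nearly doubles at r = 0.84 with 0.5 SD improvement. These sizes depend on normality, equal SDs, the assumed correlation, the assumed 15% missing and drop-outs resembling those observed. The mechanism depends only on the rule covering whole missing scores. No success criterion or sample-size figure in the protocol rests on RQ3.4.

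**What to change.** In the Analysis section, state the unit of the 20% and exclude RQ3.4 from mean replacement. Classify only clients with observed baseline and 4-month OQ-45.2 scores, and report the number not assessed in each arm. Give the proportions among those assessed. As a sensitivity bound, give them also among all randomised clients, counting those without a score first as unchanged and then as deteriorated.

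The cost is a sentence or two and one more table row. Fewer clients are classified and intervals widen slightly. In the 0.45 SD, r = 0.7 example, response on the all-randomised denominator is 30.4%, which is 5 to 6 points below the 35.7% among those assessed and the 36.2% under mean replacement. Deterioration is bounded between 5.4% (0.85 × 6.3) and 20.4% (5.4 + 15). The width of that bound is information that mean replacement hides.

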#### Proposed primary outcome measure

For research methodology feasibility measures, we will calculate screening, recruitment, randomization, and drop-out rates (RQ1.1, RQ1.2) as well as missing data in answering the outcome measures (RQ1.3). For intervention feasibility measures, we will use qualitative content analysis (QCA) [39] and/or Consensual Qualitative Research (CQR) [40, 41] to inform about the appropriateness of the VR environment to the needs of SCs, and benefits as well as barriers of VR for the use of SCs (RQ2.1, RQ2.2, RQ2.6). The facilitator’s manual adherence will be calculated using Cohen’s kappa as a robust measure of interrater reliability, in addition to the percentage (%) of the agreement between the two raters. Overall treatment integrity for each SC-VR will be calculated as the percentage (%) of treatment components defined by the manual across sessions that will be implemented as planned [42] (RQ2.3). Clients’ compliance will be assessed by the percentage (%) of seminars attempted and completed (RQ2.4). The clients’ expectancy of the SC-VR seminar, as well as potential cybersickness and the level of immersion in the VR experience, will be assessed by mean scores (M), standard deviations (SD), and 95% CI of the data gathered by using a validated 5-item [38], 7-item [36], and 15-item [37] measure (RQ2.5). Adverse events will be monitored and reported descriptively (RQ2.7).

#### Proposed secondary outcome measures

The *Outcome Questionnaire* (OQ-45.2) [25, 26] will be used to assess psychological functioning. The OQ-45.2 is a self reporting instrument that measures psychotherapeutic change over the previous week. Its total score (OQ-TOT) indicates symptom distress, quality of interpersonal relations, and social role performance. The OQ-45.2 features test–retest reliability of 0.84, excellent internal consistency at 0.93, sensitivity to change, and concurrent validity with a variety of self-report scales [25, 43, 44].

The *Questionnaire for the Evaluation of Treatment Progress (FEP-2)* [27] will be used for measuring psychological distress. The FEP-2 measures how persons feel over the previous week. Its total score (FEP-TOT) indicates well-being, symptom distress, interpersonal relationships, and congruence. The FEP-2 shows test–retest reliability of 0.77 (1 week) and internal consistency of 0.94. Concurrent validity and sensitivity to change were demonstrated.

The *Incongruence Questionnaire (INK-SF)* [28] will be used to measure motivational incongruence. Its total score (INK-SF-TOT) indicates approach goals (the maximization of desirable outcomes) and avoidance goals (the minimization of unwanted outcomes). One-week test–retest reliability was 0.81, and internal consistencies ranged from 0.75 to 0.91. Criterion validity was assessed using established instruments for psychopathological symptoms and quality of life.

The *Experience in Social Systems Questionnaire (EXIS)* [29] measures basic dimensions of what SCs aim to change in how clients experience themselves within their most important social and organizational systems (I-within-my-systems). The total score measures the clients’ experience in their personal systems (EXIS.pers) or organizational social systems (EXIS.org) containing the subdimensions of experiencing belonging, autonomy, accord, and confidence. The EXIS shows an internal consistency of 0.90. Concurrent validity and sensitivity to change were demonstrated.

A 4-point Likert scale (1 = not attained; 2 = partially attained, 3 = attained, 4 = fully attained) will be used to assess *goal attainment (GA*). At baseline, all study clients will be asked to identify their goal for the SC-VR in free text. Subsequently, clients’ goals will be classified according to the taxonomy of the Bern Inventory of Treatment Goals (BIT-T) [23] by the research team. The BIT-T encompasses five categories: coping with specific problems and symptoms (P), interpersonal goals (I), well-being and functioning (W), existential issues (E), and personal growth (G). In (re-)coding an extended sample of client treatment goals, the BIT-T proved to have a good interrater reliability, identified differences between diagnostic groups, and showed meaningful relations to standardized intake measures [24].

Clients will complete a brief *demographic measure*, including age, sex, education level, and whether they are part of a business family or a family business.

### Adverse events

Harm will be assessed by means of passive surveillance [45]. Clients will be instructed to contact the facilitators or any study team member whenever they will experience adverse events, defined as any unfavorable change in physical and/or mental condition at any time between allocation, end of the intervention, and end of study period. If necessary, clients will receive psychosocial support, including psychotherapy, in the cooperating psychotherapy outpatient Center for Mental Health and Psychotherapy (ZPP) of UW/H.

### Analysis

There will be no interim analyses. The only stopping guideline refers to the stop of recruitment 4 weeks before the start of the intervention due to organizational needs. Even if the number of participants is not reached at this time point, there will be no further recruitment at a later date. For *research methodology feasibility* measures, we will calculate screening, recruitment, randomization, and drop-out rates (RQ1.1, RQ1.2) as well as missing data in answering the outcome measures (RQ1.3) at baseline, 2-week, and 4-, 8-, and 12-month follow-up.

For *intervention feasibility* measures, we will use QCA and/or CQR to inform about the appropriateness of the VR environment to the needs of SCs and benefits as well as barriers of VR for the use of SCs (RQ2.1, RQ2.2, RQ2.6). The facilitator’s manual adherence will be calculated using *Cohen’s kappa* as a robust measure of interrater reliability, in addition to the percentage *(%)* of the agreement between the two raters. Overall treatment integrity for each SC-VR will be calculated as the percentage *(%)* of treatment components defined by the manual across sessions that will be implemented as planned [42] (RQ2.3). Clients’ compliance will be assessed by the percentage *(%)* of seminars attempted and completed (RQ2.4). The clients’ expectancy of the SC-VR seminar, as well as potential cybersickness and the level of immersion in the VR experience, will be assessed by mean scores (*M*), standard deviations (*SD*), and 95% *CI* of the data gathered (RQ2.5). Adverse events will be monitored and reported descriptively (RQ2.7).

For *estimation of effect sizes*, we will use QCA and/or CQR to analyze information about the association of these effects to either the SCs or the VR environment, or both (RQ3.1). Because clients within groups (i.e., SC-VR seminar) may be more similar to each other than clients in different SC-VR seminars, a two-level linear regression analysis will be performed to account for potential clustering effects at higher levels (i.e., clients nested within SC-VR seminars). The intraclass correlation (ICC) coefficient from the random intercept model with clients (level 1) and SC-VR seminar (level 2) will be calculated for the proposed secondary outcome (OQ-45.2) [46]. An ICC greater than zero will indicate a clustering effect, and any statistical analysis must be adjusted for this effect. All proposed outcomes will be analyzed as intention-to-treat using mean scores (M), standard deviations (SD), and 95% CI. Missing values of less than 20% will be replaced with the conditional mean value of the four subgroups (ACs in IG, and WLG; OCs in IG, and WLG). This will be compared to per-protocol analyses. We then will use mixed-design ANOVAs (group: IG, WLG; client status: AC, OC; time: baseline, 2-week and 4-month follow-up), adjusting for baseline scores considering demography as well as outcome data. Because treatment outcome will be measured at three assessment points, within-group effects will be further analyzed by comparisons between baseline and 2-week follow-up (contrast A), and by comparisons between 2-week and 4-month follow-ups (contrast B). Effect sizes will be presented as partial eta-squared values (η^2^) and Cohen’s *d*, calculated as the difference between the means divided by the pooled standard deviation $$(d=\frac{{x}_{1}^{2}-{x}_{1}^{2}}{\frac{\sqrt{{s}_{1}^{2}+{s}_{2}^{2}}}{2}})$$. Classification of *effect sizes* will be as follows: η^2^ ≥ 0.010, small effect; η^2^ ≥ 0.060, medium effect; η^2^ ≥ 0.140, large effect; Cohen’s *d* ≥ 0.20, small effect; *d* ≥ 0.50, medium effect; and *d* ≥ 0.80, large effect [47] (RQ3.2, RQ3.3). The exploration of *reliably significant change*, i.e., the proportion of remission, response, deterioration, and no change, will be limited to the proposed secondary outcome (OQ-45.2) based on the reliable change index (RCI) [48]. We will use previously established internal consistency reliabilities to calculate the RCI [49] and Jacobson and Truax’s [48] cutoff C for the categorization of the clients’ (no) change [26–28] (RQ3.4).

For *qualitative data analyses*, we collect qualitative information for in-depth analysis of the appropriateness of the VR environment to the needs of SCs, benefits as well as barriers of VR for the use of SCs (RQ2.1, RQ2.2, RQ2.6), and to analyze information about the association of SC-VR effects to either the SCs or the VR environment (RQ3.1). We will perform semi-structured interviews with the participants. The qualitative data will be interpreted based on QCA [37] and/or CQR [43].

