
## Methods

### Design

The study is designed as a prospective, monocentric, parallel-group, feasibility RCT with subsequent intervention. A total of 128 clients of group-based SCs in VR-seminars will be randomized to either the intervention group (IG, *n* = 64) or wait-list group (WLG, *n* = 64). Each study facilitator will conduct four SC-VR seminars in tandem-partnership. The short-term intervention outcome will be measured including three assessment points: baseline and 2-week and 4-month follow-up, with the latter representing the primary endpoint. In addition, we will assess mid-term effects at 8-month follow-up and long-term effects at 12-month follow-up.

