### Sample size calculation

Although feasibility studies, e.g., to develop an intervention, do not require a sample size calculation, it was important for us to ground the number of participants in our study on a statistical rationale that would allow a statement to be made about the sample size needed for a confirmatory trial. Cocks and Torgerson [31] used a confidence interval (CI) approach to calculate pilot sample sizes for continuous outcome measures. Supposed 0.3 of a standard deviation between two groups would be worthwhile, then such a study requires about 350 clients (assuming 80% power, two-sided alpha of 5%) in the final analysis of the fully powered RCT. Consequently, 32 clients (approximately 9% of the main sample size) would be required to produce a one-sided 80% confidence limit. A pilot trial with that sample size which finds an estimate larger than zero is supposed to demonstrate feasibility of a confirmatory RCT considering the recruitment and retainment of clients and so forth. According to this approach for two-arm feasibility RCTs, we will recruit a minimum of 32 clients. Since we are in the good position of sufficient personal and financial resources, we can include more clients in our study, and if possible, we will recruit 128 individuals, i.e., 64 clients in the IG and WLG, respectively (Fig. 1).

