### Biases and limitations

This trial is a feasibility study, and all statistical analyses will be descriptive and explorative, with the aim to obtain data that can then be used for planning a subsequent confirmatory RCT. Consequently, the main RCT is necessary before any confirmatory statement about the efficacy of SCs in VR can reliably be made. We will use a WLG design instead of an active control group treatment [50]. We will select only four study facilitators: their long-term experience and expertise in conducting SCs also limits generalizability. Their allegiance to the treatment, a factor known to contribute to the outcome regardless of the specific intervention [51], may be high. Therefore, our results have to be discussed in terms of facilitator allegiance. Although investigators will not proponents of the SC approach, four of the six authors are systemic therapists or counselors; thus, their presence as researchers in the SCs can also influence the group process and the proposed outcomes.

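### Clustering adjustment hangs on the sign of one noisy ICC estimate, and the two-level regression, the ICC rule and the ANOVA (no seminar term, baseline used twice) are not reconciled

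*Protocol article*

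**What the plan says.** Three statements on clustering stand in the Analysis section of the protocol article, in the paragraph on estimating effect sizes.

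1. A two-level linear regression, with clients nested in seminars, will be performed to account for clustering. No condition is attached.
2. The ICC from a random-intercept model will be calculated for OQ-45.2, followed by the rule "An ICC greater than zero will indicate a clustering effect, and any statistical analysis must be adjusted for this effect".
3. The model for the outcomes is then given: "We then will use mixed-design ANOVAs (group: IG, WLG; client status: AC, OC; time: baseline, 2-week and 4-month follow-up), adjusting for baseline scores". The adjustment is said to cover demography and outcome data. No seminar factor is listed, and the text does not say how the ANOVA would be adjusted.

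The number of seminars is not stated in the text, and Figure 1 is not shown. The Design section says "Each study facilitator will conduct four SC-VR seminars in tandem-partnership", and Biases and limitations says "We will select only four study facilitators". The WLG receives its seminar only after 4 months (Abstract, Design).

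**The concern.** Clients who share a 3-day group seminar and its facilitators are likely to have correlated outcomes. Whether the analysis allows for this should follow from the design and not from the sign of an estimate based on a handful of seminars. Here a single estimate, from one outcome, decides for every analysis, and the ANOVA named afterwards has no place for the seminar.

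Two further features matter. Up to 4 months only IG clients have attended a seminar, so nesting all clients in seminars mixes clustered and unclustered arms in one ICC. And baseline is both a level of the time factor and a covariate, so the group main effect averages in a time point at which the adjusted group difference is zero by construction.

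At stake are the confidence intervals, effect sizes and ICC that this feasibility trial is meant to hand to the confirmatory RCT.

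**Working it through.** **The plan's own figures.** The Sample size calculation section takes a standardised difference of 0.3 ("Supposed 0.3 of a standard deviation between two groups would be worthwhile") with 80% power and two-sided alpha of 5%. Per arm: 2 × (1.960 + 0.842)² / 0.3² = 174.4, so 175, total 350. The pilot minimum is 4 × (0.842 / 0.3)² = 31.5, so 32; likewise 9% × 350 = 31.5. Both figures reproduce, and neither contains a design effect, so any allowance for seminars has to come from the ICC estimated in this trial.

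**Inputs for the check.**
- Seminars: 4 facilitators × 4 seminars / 2 per tandem = 8; 128 / 8 = 16 clients each; 4 seminars in the IG (k = 4, m = 16). If each facilitator leads four separate seminars, there are 16 of 8 clients. The text fixes neither.
- ICC: the article gives no value. Assumed range 0.02 to 0.10.
- Clustering up to 4 months in the IG only, because the WLG is untreated.

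**How well the sign of the ICC discriminates.** The estimate is zero or less when the between-seminar mean square does not exceed the within-seminar one. Its probability is the F distribution function at (1 − ICC) / (1 + (m − 1) × ICC), with k − 1 and k(m − 1) degrees of freedom. For the 4 IG seminars at ICC 0.05 this is F(0.95 / 1.75; 3, 60) = 0.345; simulation (20,000 runs) gave 0.344. At ICC 0.02 it is 0.476, and at 0.10 it is 0.218. With a true ICC of 0 the estimate is positive with probability 0.40 (4 IG seminars) or 0.43 (all 8). For 8 IG seminars of 8, the probability of zero or less at ICC 0.05 is 0.331, so that layout does not rescue the rule.

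**Cost where no adjustment is made.** IG design effect = 1 + (m − 1) × ICC. With one clustered arm the variance ratio is (design effect + 1) / 2. The type I error is 2 × [1 − Φ(1.96 / √ratio)].

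| Assumed IG ICC | IG design effect (m = 16) | Correct SE / reported SE | Error at nominal 5% |
|---|---|---|---|
| 0.02 | 1.30 | 1.07 | 6.8% |
| 0.05 | 1.75 | 1.17 | 9.5% |
| 0.10 | 2.50 | 1.32 | 13.8% |

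With seminars of 8, the error at ICC 0.05 is 7.1% and at 0.10 it is 9.2%. In simulation, among the trials in which an estimate of zero or less led to no adjustment (m = 16), the error was about 9% to 10% at ICC 0.05 and about 14% to 15% at 0.10.

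**Error if the rule is obeyed.** Unadjusted t-test when the estimate is zero or less, otherwise a test on seminar means: overall type I error was about 3% to 3.5% at ICC 0, 4% to 5% at 0.05 and 5% to 5.5% at 0.10.

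**ICC with untreated WLG clients included.** At an IG ICC of 0.05 the expected between-seminar mean square averages (1.75 + 1) / 2 = 1.375 and the within-seminar one (0.95 + 1) / 2 = 0.975. The pooled ICC is (1.375 − 0.975) / (1.375 + 15 × 0.975) = 0.025 (simulated mean 0.024), half the IG value. The IG design effect would then be read as 1 + 15 × 0.025 = 1.375 instead of 1.75.

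**Baseline twice.** The mean over three times is (baseline + week 2 + month 4) / 3. After adjustment for baseline, the baseline term contributes nothing, so the estimate is 2/3 of the mean follow-up effect. Its standard error is also 2/3, so F and partial eta-squared are unchanged. Simulation (8,000 runs; assumed correlation 0.6, effect 0.50 SD at both follow-ups) gave 0.333 with three times and 0.499 with the two follow-ups; both rejected in 98.6% of runs. Without the covariate the three-time estimate was also 0.332. The group-by-time test kept its size (4.9%).

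**The case against.** A reader might infer that clustering is handled only if the ICC exceeds zero, or not at all. The text does not support that: the two-level regression is announced without condition, and the word any in the ICC rule takes in the ANOVA. What remains is that the article does not say which model yields the results or how the ANOVA takes up the adjustment.

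A reader might also infer that standard errors are too small throughout. They are too small only if the ANOVA is run as listed, or in a trial where adjustment is skipped although clustering exists. Under the rule as written, overall type I error stays near nominal. That average covers two unequal parts: conservative results where clustering is found by chance, and inflated ones where it is missed.

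A third tempting reading is that double use of baseline dilutes the treatment effect. The shrinkage to two thirds comes from baseline being a level of time and appears without the covariate too. Group × time, partial eta-squared and a Cohen's d at a single time point are not diluted, and RQ3.2 and RQ3.3 ask for change from baseline to 4 months. Only the raw group main effect is affected.

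The low-ICC point is conditional as well. The article names no time point for the ICC, and the note to Table 1 schedules a WLG assessment 2 weeks after its own seminar, so treated data from both arms will exist. Even a halved ICC does no harm if it is applied to both arms of another wait-list trial with seminars of the same size, since 1.375 is also the correct variance ratio there. It does understate the need if applied to the IG alone, or to the active-control design that the Discussion also considers if both arms then meet in groups.

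Finally, the analyses are explorative, OQ-45.2 is a secondary outcome, and model details may be left to an analysis plan. That lowers the severity, but the article does fix a decision rule and a list of factors, and these do not fit together.

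**Conclusion.** The concern holds in a limited form. The regression, the ICC rule and the ANOVA need to be reconciled, and the sign of an estimated ICC is a poor switch: at an assumed IG ICC of 0.05 it misses clustering in about 34% of trials, and with no clustering it signals it in about 40% to 43%. Where adjustment is then left out, the correct standard error is about 17% larger than the one reported, and the nominal 5% error is about 9% to 10% (about 14% at ICC 0.10). Across the rule as a whole, error is roughly 3% to 5.5%.

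An ICC computed up to 4 months with untreated WLG clients nested in seminars would be about half the IG value. The raw ANOVA group main effect is two thirds of an effect that is constant over both follow-ups.

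These sizes rest on assumed ICCs and on an inferred layout of 8 seminars of 16; with 16 seminars of 8 the inflation is smaller. Severity is moderate: no confirmatory claim depends on this, but the intervals and planning inputs for the confirmatory RCT do.

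**What to change.** Drop the ICC-above-zero condition and name one model for every outcome in place of the regression-plus-ANOVA sequence:

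- outcome: the 2-week and 4-month scores, with the baseline score and client status (AC or OC) as covariates;
- fixed effects: group, time and group × time;
- random effects: client, and seminar for IG clients (partially nested), kept whatever the ICC estimate;
- small-sample degrees of freedom (Kenward-Roger or Satterthwaite).

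Report the group difference at each follow-up. Report the ICC from treated clients only, with its 95% CI, and state the time point and the number and size of seminars behind it.

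The cost is a change of wording and no new data. Intervals will be wider (by about 17% at ICC 0.05 and 32% at 0.10 with seminars of 16) and will rest on fewer degrees of freedom. With so few seminars the ICC interval will be wide, which is itself useful to whoever plans the confirmatory RCT.
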